### **4. (exploratory): How long do neural and symptom changes last after mbNF + DBT?**

We hypothesize that changes in neural connectivity and decreases in BPD symptom severity will last for several months after mbNF. We will explore the durability of observed changes using linear mixed-effects models testing for group (mbNF vs. controlNF) x timepoint (pre-NF to post- NF, 5 timepoints during DBTsg, and at 1- and 2-month post-DBT follow-up timepoints) in symptom change (primary: BSL23; secondary: SMS). Models will include a random effect for subject and fixed-effect covariates (e.g., age, sex, site, baseline symptoms).

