### **3.3 Secondary Objective**

The secondary objectives of this study are:

- 1) To explore whether mbNF (compared to control NF) increases mindfulness in adults with BPD
- 2) To explore whether mbNF-mediated neural and symptom changes persist after the end of mbNF and psychotherapy.

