### **4.2.2 Secondary and Exploratory Outcome Variables**

1. Mindfulness will be measured by the State Mindfulness Scale, a 21-item self-report measure that quantifies current-moment mindfulness of body and mind.
2. Whether neural and clinical changes persist will be measured at follow-up time points using the primary outcome variables

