### **1. Target Engagement: DBT with mbNF will change resting-state DMN connectivity toward a more mindful brain state.**

We will test if mbNF leads to larger changes than control-NF (medium effect-size  $d \geq 0.5$ ) in at least one of our two DMN connectivity targets. We will calculate within-subject change from pre- to post-NF, then use one-tailed t-tests (mbNF vs. controlNF) to test our hypothesis that mbNF will lead to larger change by decreasing within-DMN connectivity and/or increasing DMN-FPCN anticorrelation. This effect size is in line with our prior mbNF research in other patient groups (where we saw effect sizes of  $d=0.7$  to  $d=0.91$ ).

**2. Our primary clinical outcome is change in BPD symptom severity (BSL23 survey score) in the full study sample (62/group). Our secondary outcome is change in current-moment mindfulness (SMS score).** For each outcome, we will test the hypothesis that mbNF+DBTsg will decrease score more than control-NF+DBTsg from baseline (pre-NF) to primary endpoint (DBTsg week 16) using a linear mixed regression model with group (between-subject) x time (within-subject) interaction. Based on previous work, we expect significant medium-large effects. Correlation between repeated observations within-subject will be modeled with structured variance-covariance and/or random subject effects. The best-fitting model will be chosen based on information criteria. Least-square (LS) means will be compared and plotted post-hoc to examine significant effects. Power Analysis: Using G\*power, we estimate achieving 80% power to detect small effects ( $f=0.15$ ) with 62 subjects in each of two groups, two timepoints,  $p=0.05$ , correlation among measures 0.3, and sphericity assumed.

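### The only test named for durability asks whether the arm difference varies across visits, not whether a difference remains at follow-up, so a significant result is not evidence of persistence

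*Protocol*

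**What the plan says.** Section 3.3 of the protocol sets the second secondary objective: "To explore whether mbNF-mediated neural and symptom changes persist after the end of mbNF and psychotherapy". Section 4.2.2 says where this is to be read: "Whether neural and clinical changes persist will be measured at follow-up time points using the primary outcome variables".

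Section 5.4.1, item 4, labelled exploratory, carries the analysis. Its hypothesis is directional: "We hypothesize that changes in neural connectivity and decreases in BPD symptom severity will last for several months after mbNF". Its method is: "We will explore the durability of observed changes using linear mixed-effects models testing for group (mbNF vs. controlNF) x timepoint". The visits listed are pre-NF, post-NF, "5 timepoints during DBTsg, and at 1- and 2-month post-DBT follow-up timepoints", which makes nine. On structure it adds: "Models will include a random effect for subject and fixed-effect covariates". It names no contrast at the follow-up visits and does not say whether timepoint is a category or a linear trend.

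Two sentences elsewhere in section 5.4.1 bear on this. The data preparation paragraph says that conclusions will rest mainly on effect sizes with 95% confidence intervals rather than on significance. Item 2, on the week-16 outcome, plans post-hoc comparison of least-squares means.

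**The concern.** Persistence of an mbNF effect means that the arms still differ, in change from pre-NF, at the 1- and 2-month visits. The null hypothesis that matches this question is no arm difference in that change at follow-up.

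The named test has a different null. With timepoint as a category, the group x timepoint interaction is zero when the arm difference is the same at all nine visits. Randomised arms are expected to be equal at pre-NF, so any later separation makes this null false, including one that appears only during DBTsg and is gone a month later. A benefit that disappears also adds variation between visits, which raises the test statistic.

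A significant interaction could therefore be reported under a durability heading when nothing is left at follow-up. A benefit that appears early and stays constant could be missed by the same test.

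**Working it through.** **Inputs from the protocol.** Item 2 of section 5.4.1 states "we estimate achieving 80% power to detect small effects ( $f=0.15$ ) with 62 subjects in each of two groups", with two timepoints, alpha 0.05, correlation 0.3 and sphericity. Item 4 gives no power figure, so these inputs are carried over to its nine visits.

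**Reproducing the stated figure.** For the repeated-measures interaction, λ = N·m·f²/(1−ρ) = 124 × 2 × 0.0225 / 0.7 = 7.97 on 1 and 122 df. Power is 0.800, as stated. With two groups and two timepoints, f equals a quarter of the arm difference in change, so f = 0.15 is 4 × 0.15 = 0.6 SD. This is the reference effect below.

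**The item 4 test.** Assume compound symmetry (which a random subject effect implies), SD 1 and complete data. For an arm-difference profile δ over T visits, λ = (n/2)·Σ(δ_t − mean δ)²/(1−ρ), on T−1 and (T−1)·122 df. With T = 9, n = 62 and ρ = 0.3, this is λ = 44.29 × Σ(δ_t − mean δ)² on 8 and 976 df.

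The profiles are assumptions. The order is pre-NF, post-NF, five DBTsg visits, 1 month, 2 months.

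| Profile (SD) | Σ(δ_t − mean δ)² | λ | Significant |
|---|---|---|---|
| Builds, fully lost: 0, 0, 0, 0.2, 0.4, 0.6, 0.6, 0, 0 | 0.56 | 24.8 | 97% |
| Builds, fully retained: 0, 0, 0, 0.2, 0.4, 0.6, 0.6, 0.6, 0.6 | 0.64 | 28.3 | 98% |
| Flat 0.6 from post-NF, lost at both follow-ups | 0.72 | 31.9 | 99% |
| Flat 0.6 from post-NF, retained | 0.32 | 14.2 | 77% |
| Flat 0.5, lost at both follow-ups | 0.50 | 22.1 | 94% |
| Flat 0.5, retained | 0.22 | 9.8 | 58% |

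In the first pair the test hardly distinguishes loss from retention. In the flat pairs it rejects more often when the benefit has gone.

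**Sensitivity to size.** Scaling the building-then-lost profile to other peaks gives 86% at 0.5 SD, 64% at 0.4, 37% at 0.3 and 17% at 0.2. With the last DBTsg visit dropped (eight visits), the figures from 0.6 down to 0.2 SD are 87%, 69%, 47%, 26% and 13%.

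**Limits of the test's sensitivity.** A difference at one visit only is detected with power 11% at 0.2 SD, 58% at 0.5 and 77% at 0.6. An equal difference at every visit, pre-NF included, gives 5%.

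**If timepoint were a linear trend.** Take assumed visit weeks −4, −3.5, 0, 5, 10, 15, 20, 24, 28 and an early effect that fades (0, 0.6, 0.6, 0.45, 0.3, 0.15, 0, 0, 0). The slope difference is significant in about 91% of trials, with a sign that shows fading. A significant slope alone would not show persistence either.

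**A contrast aimed at the question.** For the arm difference in change from pre-NF to the mean of the two follow-ups, SE = √[(2/62) × 0.7 × (1 + 1/2)] = 0.184 SD. It rejects in 5% of trials under full loss. Its power is 90% if 0.6 SD is retained and 37% if 0.3 SD is retained. Using the 2-month visit alone, SE = √[(2/62) × 0.7 × 2] = 0.213 and power at 0.6 SD is about 80%.

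**The case against.** The strongest reply is that item 4 is exploratory and sets no success criterion, and that the protocol intends to conclude from estimates and intervals rather than p-values. How long an effect lasts is also a question about a trajectory, which needs all visits in the model. With categorical timepoint the fitted model already contains the arm difference at each follow-up visit, and choosing the contrast for an exploratory aim is often left to the SAP.

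Much of this stands. The model, visits and data are sound and need not change. A reader might infer that the objective cannot be answered at all; that does not follow, because the same model can yield the follow-up estimates. A reader might also infer that a vanished effect would pass as durable, but the protocol contains no pass rule. Nor is the interaction significant whenever the arms differ at some visit. The difference must vary across visits, and small or single-visit differences are often missed. With a linear trend, the sign of the slope would reveal an early effect that faded.

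What does not stand is that the other sentences cure the mismatch. An interaction on eight degrees of freedom has no single effect size or interval for persistence, and item 4 names no follow-up estimate to report. The least-squares means sentence belongs to item 2, is post hoc and mentions no follow-up visit. The point does not concern detail left out for a SAP: the protocol names a test, and its null is not the one that sections 3.3 and 4.2.2 call for.

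**Conclusion.** The concern holds in a limited form. The test named for durability does not isolate the follow-up visits, and its significance should not be read as persistence. At the 0.6 SD effect implied by the protocol's own power statement, it is significant in 97% to 99% of trials when the benefit is fully lost and in 77% to 98% when it is fully retained, for the two profile shapes examined.

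These figures rest on assumed visit profiles, compound symmetry, no missing data, and planning inputs borrowed from item 2. They do not support saying that any trial with a real week-16 effect would almost always show a significant durability test: for the building profile the rate drops to 37% at a lost peak of 0.3 SD and 17% at 0.2 SD. The mismatch between test and question does not depend on these numbers. The exploratory label limits the consequence but does not remove it, since no other analysis is named for this secondary objective.

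**What to change.** In section 5.4.1, item 4, state that timepoint is categorical. Name as the durability estimate the arm difference in change from pre-NF to follow-up, with its 95% CI. Either the average of the 1- and 2-month visits or each visit separately would serve, provided the choice is made in advance. State that the overall group x timepoint interaction is descriptive and is not cited as evidence of persistence.

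This takes about one sentence in the protocol and a matching line in the SAP, with the same model and data. It also gives the plan's preference for effect sizes with intervals a specific quantity to report. The downside is modest power when only part of the effect is retained: about 37% at 0.3 SD for the averaged contrast, against 90% at 0.6 SD.

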### ***Rigor and Reproducibility***

The proposed study will take a number of steps to ensure reproducibility and rigor: (1) ensuring sufficient power; (2) administering reliable, valid, and developmentally appropriate assessments; (3) including age cutoffs to minimize variability of differences in brain function and disease phase due to late life changes in neural function; (4) creating a detailed statistical plan; (5) recruiting a representative sample, increasing the generalizability of findings; and (6) facilitating external reproducibility as de-identified data will be placed in the NDA

### 5.4.2 Analysis of Subject Characteristics

*Sex as a Biological Variable* The extent of sex differences in the neurobiology and behavioral expression of BPD remain unclear. We will test sex differences in all variables as well as sex as a moderator of key predictors. Given well-established sex differences in the frequency of patients being given the BPD diagnosis and presentation for mental healthcare (despite likely-similar community prevalence), we expect that our sample will be ~80% female. Although not our main aim, we will provide important preliminary results regarding sex differences in response to mbNF.

*Site Differences* Though we aim to minimize site differences in sociodemographic factors, we will probe potential differences and control for these in analyses. To further control for potential differences between the two sites, we will implement ComBat harmonization to remove site-related variance in connectivity measures. ComBat has been shown to facilitate reliable and efficient analysis, accounting for non-biological, scanner-specific sources of variability, in multi-site fMRI neuroimaging studies. Additionally, all analyses will include a main effect of site, and we will examine potential first-order site x time and site x group x time interactions.

To further understand effects for the neural and clinical targets, we will control for key covariates (e.g., age, sex, site, head motion, clinical and demographic variables that differ between groups), and explore the impacts of mbNF vs. controlNF on the use of mindfulness skills and DBT skills from each module in daily life, DBTsg group attendance, and use of mental healthcare resources outside the study. We will also relate acceptability and tolerability data from program evaluation to attendance and dropout data.

As an exploratory analysis of broader modulation within the DMN, we will test within-DMN connectivity between other common nodes, i.e. posteromedial cortex, angular gyrus, lateral and medial temporal cortex. Furthermore, to explore the spatial specificity of our findings, we will perform this model on DMN connectivity voxel-wise (mPFC seed) across the brain using Threshold Free Cluster Enhancement (TFCE) for multiple comparisons correction.

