#### 4.3.2 Eligibility Criteria/Vulnerable Populations

As above, we plan for 124 people to complete the overall study. We expect that enrollment will be balanced between the New Haven and Boston cohorts, for a total of 62 participants per site. This means that we expect a final total of 31 completers randomized to each group (mbNF and control NF) at each site at the end of the study.

This study is open to people of any sex at birth and any gender.

**Inclusion criteria.** All subjects must: be age 18-60, be able to provide written informed consent, meet criteria for BPD on semi-structured clinical interview, be able to plan to keep any prescribed medications and psychotherapy constant during the study, and be fluent in English.

**Exclusion criteria.** Potential subjects will be excluded for:

- current DBT psychotherapy outside the study
- lifetime primary psychotic disorder or Bipolar I disorder
- developmental disorder (e.g. autism)
- history of learning disorder
- moderate or severe substance use disorder in the last 6 months
- active suicidal ideation with intent or plan in the past 3 months
- history of major medical or neurologic disorder
- MRI contraindications, including pregnancy
- poor performance on reading task (WRAT > 11 errors)
- newly prescribed medications in the past 8 weeks
- daytime sedating medications (e.g. benzodiazepines, opiates, sedating neuroleptics)
- any scheduled daily benzodiazepines
- change in psychotherapy type or frequency in the past 12 weeks.
- At the discretion of the study PI

*Termination criteria.*

- Enrolled participants will be terminated from DBT group participation for:
  - Missing over 3 consecutive DBT group sessions. These participants will still be invited to complete study assessments.
- Enrolled participants may be terminated from the study:
  - At the discretion of the study PI

Eligibility will be determined by study personnel.

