**Randomization and control condition**

Subjects assigned to receive NF at each site (Yale and MGH) will be randomized within-site using a predetermined randomization schedule prepared and known only to the site neuroimaging staff (the rest of the study staff will remain blinded). Each schedule will result in 1:1 randomization with the constraint that the number of mbNF cases is always  $\geq$  the number of control-NF cases (necessary to ensure each control subject has a prior mbNF subject to be matched to) and also the constraint that the number of mbNF cases does not exceed the number of control-NF cases by more than three (to keep the two groups reasonably balanced over time). Clinical staff and assessment raters will remain blind to group assignment. Subjects will be debriefed at the end of the study and at that time their group assignment will be disclosed.

**Yoked-sham feedback** Subjects in the control-NF group will complete the mindfulness training and undergo similar MRI scan procedures. The primary difference in scans is that the control-NF subjects will not receive feedback based on their own brain's activity but will receive feedback based on data extracted from a previously-acquired mbNF session with a different study subject. Thus, the visual display will be independent from the subject's own brain activity in the control-NF group. This ensures that subjects across groups are viewing equivalent stimuli. This yoked sham control approach was chosen for this study because it allows for subject blinding, creates a similarly engaging feedback training experience, and balances positive feedback received across groups. Specifically, a control-NF subject receives feedback indicating they are having the same amount of success as the NF subject they are yoked to. The perception of success can impact motivation because it is easier to stay motivated if the participant feels they are having some success. It is also likely to affect

the magnitude of the placebo effect, because if a participant sees that they are successful in controlling their mindfulness-related brain patterns, they are likely to have a larger placebo effect. Thus, controlling for perception of success is critical.

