## 5.4 Statistical Method

### 5.4.1 Statistical Design, Sample size determination, and Planned Analyses

*Data Preparation* Data will be examined for outliers, non-normal distributions, and non-linear associations. Preliminary analyses will examine potential covariates including site, age, sex, clinical variables, and head motion. We will explore the presence of group effects (and time effects when appropriate) across individual covariates or combined factors across multiple covariates using a liberal  $p < .05$  uncorrected threshold and include any suprathreshold variable as control covariate in subsequent analyses. Detailed information regarding psychiatric service use (e.g., therapy, medication, unplanned mental health service use) will be assessed to test whether this differentially impacts (or is affected by) change in our neural targets. We will also explore baseline symptoms as a potential covariate in the analyses. Conclusions will primarily be based on effect sizes with 95% confidence intervals rather than statistical significance to maximize reproducibility. Based on our prior studies, we estimate ~30% attrition/data loss. We have planned for adequate initial recruitment to anticipate complete data to include 124 subjects.

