### 5.4.3 Interim Analysis

This project is expected to be funded by the NIMH through the R61/R33 mechanism. This mechanism has a go/no-go decision after two years (the R61 phase). For the GO criterion, we will test if mbNF leads to larger changes than control-NF (medium effect-size, Cohen's d of at least 0.5) in at least one of our two DMN connectivity targets. We will calculate within-subject change from pre- to post-NF, then use one-tailed t-tests (mbNF vs. shamNF) to test our hypothesis that mbNF will lead to larger change by decreasing within-DMN connectivity and/or increasing DMN-FPCN anticorrelation. This analysis will include all of the R61 participants who complete the neurofeedback day (n = 26 per group).

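### Site is the randomisation stratum, but the only site term committed to the analyses is a main effect, which drops out of the primary group x time test; site x time should be committed instead

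*Protocol*

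**What the plan says.** - **Design.** Under Randomization and control condition (Protocol 5.1), participants "will be randomized within-site using a predetermined randomization schedule", with a limit on imbalance: "the number of mbNF cases does not exceed the number of control-NF cases by more than three". Section 4.3.2 expects "31 completers randomized to each group (mbNF and control NF) at each site".
- **Site control.** Section 5.4.2, Site Differences: "Additionally, all analyses will include a main effect of site, and we will examine potential first-order site x time"; the sentence goes on to site x group x time. The same paragraph applies ComBat harmonisation to the connectivity measures.
- **Primary clinical test.** Section 5.4.1, item 2, tests BSL23 (and SMS as secondary) from pre-NF to week 16 "using a linear mixed regression model with group (between-subject) x time (within-subject) interaction". No site term is named.
- **Connectivity and GO tests.** Item 1 takes pre- to post-NF change, "then use one-tailed t-tests (mbNF vs. controlNF) to test our hypothesis". Section 5.4.3 does the same for the go/no-go decision, "then use one-tailed t-tests (mbNF vs. shamNF) to test our hypothesis". Item 3 is a Pearson correlation. None of these names site.
- **Covariate screen.** Section 5.4.1, Data Preparation: "Preliminary analyses will examine potential covariates including site, age, sex, clinical variables, and head motion". A variable is carried forward if it shows a group effect, or where appropriate a time effect, at an uncorrected 5% level.

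**The concern.** An analysis should follow the stratification used in the randomisation. Three things stand in the way here.

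1. The committed term acts on the wrong quantity. A group x time test compares change between arms. A site main effect moves a participant's level equally at both visits and leaves change alone.
2. The general rule in 5.4.2 does not fit the tests named elsewhere. A two-sample t-test and a Pearson correlation have no place for a site term, so an analyst cannot follow both instructions literally.
3. Section 5.4.2 always includes site, while 5.4.1 includes it only if it passes a screen. With 1:1 allocation within site and imbalance capped at three, site can hardly be associated with group, so the group part of that screen would rarely keep it.

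At stake is precision. Any site difference in mean change stays in the error variance of the primary comparison.

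**Working it through.** **The plan's own power figure.** Inputs from 5.4.1, item 2: f = 0.15, N = 124, two timepoints, correlation 0.3, alpha 0.05.

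- Noncentrality = f² × N × 2 / (1 − 0.3) = 0.0225 × 124 × 2 / 0.7 = 7.97. On F(1, 122) the power is 0.7999, so the stated 80% reproduces.
- The same effect on the change score is d = 4 × 0.15 / √(2 × 0.7) = 0.507.

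**Why the main effect cancels.** Write the outcome as b0 + b1·group + b2·time + b3·group·time + b4·site + u + e, with u the participant effect. Week 16 minus baseline is b2 + b3·group + (e1 − e0). Both b4·site and u are gone. A site x time term adds c·site to the change, which is the adjustment wanted.

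**Numerical check.** Random-intercept models were fitted by REML to simulated data: 124 participants, correlation 0.3, sites assumed to differ by 0.5 SD at baseline and by 0.5 SD of change.

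- Complete data: adding the site main effect moved the group x time estimate by less than 1e-14 and its SE by about 0.002%. This held with equal cells and with cells of 33/30 and 31/30.
- Complete data: adding site x time cut the SE by about 2.5%.
- 30% of week-16 values missing: the main effect moved the estimate by up to 0.09 outcome SD and the SE by up to 2%. Site x time cut the SE by about 3.5%.

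**Cost of leaving site off the change.** Let δ be the site difference in mean change, in within-site SDs of change. The documents give no value, so δ is an assumption. With equal sites and balanced arms, the variance used by the unadjusted test is inflated by 1 + δ²/4: 1.01, 1.0625, 1.16 and 1.25 at δ = 0.2, 0.5, 0.8 and 1.0. The arm difference itself does not vary more, because each site contributes equally to both arms. Only the estimated SE grows, so the test is conservative. Simulation of the change-score test (100,000 replicates, 31 per cell, d = 0.507):

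| δ (assumed) | Type I, no site | Type I, with site | Power, no site | Power, with site |
|---|---|---|---|---|
| 0 | 0.050 | 0.050 | 0.801 | 0.800 |
| 0.2 | 0.049 | 0.050 | 0.796 | 0.799 |
| 0.5 | 0.042 | 0.048 | 0.779 | 0.797 |
| 0.8 | 0.036 | 0.051 | 0.756 | 0.802 |
| 1.0 | 0.028 | 0.050 | 0.728 | 0.801 |

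**ComBat.** In one illustrative data set, removing an additive site offset left the t statistic on connectivity change at −2.731. Adjusting location and scale together moved it to −3.103. The additive part therefore cancels in change scores, and the scale part does not. Neither touches BSL23 or SMS.

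The effect of omitting site from the item 3 correlation was not quantified.

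**The case against.** A reader might infer that the plan's site control acts on none of the main comparisons. The documents do not support that.

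- Section 5.4.2 also examines site x time and site x group x time, and applies ComBat, whose scale adjustment can alter the connectivity tests and the correlation.
- The screen in 5.4.1 allows for time effects, so a site difference in change might bring site in by that route.
- If the rule in 5.4.2 is taken to override the short test descriptions, a site term in a model of change is the same thing as site x time and does act.
- The cancellation is exact only with complete data, and 5.4.1 expects about 30% attrition or data loss, although it plans recruitment to reach 124 with complete data.

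All of this stands. It does not remove the point: for BSL23 and SMS the term that adjusts change is never committed, and the reader must choose between conflicting instructions for the other tests.

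A reader might also infer that the primary estimate could become a single-site estimate. That needs the three-way term kept in the primary model, 0/1 coding of site, and the raw coefficient reported as the treatment effect. The plan states none of these.

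Nor is there a case for bias in the treatment comparison, given the planned balance within site.

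Finally, a large δ for BSL23 is hard to motivate. Section 4.1.3 has one site do all recruitment and assessment, usually remotely, and one centre give remote therapy to everyone, so site is mainly scan location and metropolitan area. That argues for the upper rows of the table.

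**Conclusion.** The point holds as an internal inconsistency and a modest loss of efficiency. The committed site term drops out of the primary clinical contrast with complete data and has only an incidental effect with missing endpoints. The wording for the t-tests, the correlation and the covariate screen conflicts with the rule in 5.4.2. The power loss runs from under half a point at δ = 0.2, through about 2 points at 0.5, to about 7 points at 1.0. It rests on the assumed δ, about 31 per cell, and the plan's own f and correlation. The estimate is not biased and type I error is not inflated. The change is still worth making, because the planned power is 0.7999 and has no margin.

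**What to change.** 1. Section 5.4.1, item 2: commit site x time as a fixed term in the BSL23 and SMS models, or use site in a baseline-adjusted model of the week-16 score.
2. Section 5.4.1, item 1, and 5.4.3: analyse connectivity change with a linear model on group plus site. Keep the same one-sided contrast and the same definition of d, so that the GO threshold does not move.
3. Section 5.4.1, item 3: use a partial correlation given site.
4. Section 5.4.1, Data Preparation: take site off the list of screened covariates.
5. Section 5.4.2: state that site x group x time is examined only in a separate sensitivity model.

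The cost is a few words and one degree of freedom per model. At every δ tried, the site-adjusted test has type I error of about 0.05 and power of about 0.80, and at δ = 0 it loses nothing measurable.
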